### Blinding

The participants, the occupational health professionals and the researcher are not blinded for the group assignment. It is likely that several participants of one department will participate and therefore knowledge about both groups is provided for the participants. Furthermore, OPs will be visited by both employees in the workplace intervention group and employees in the usual care group. Therefore they cannot be blinded. Since all follow-up questionnaires are sent to the employee by mail, no direct influence by the researchers or occupational health professionals is likely to occur.

The registration of sick leave in the Netherlands is done by companies and managed by the occupational health services. Since these measurements are extracted from computerized databases, bias caused by a lack of blinding is prevented for this outcome. Since the secondary outcomes are all self-reported, blinding is impossible. After randomisation all participants receive a research code consisting of a consecutive number. A research assistant will put all data in the computer by the research code. Therefore, the analysis of the data by the researcher will be blind.

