#### Consult OP

All employees consult the OP before the intervention starts. In this consult the guidelines for usual care are followed. The OP instructs the inventory for stressors to participants as a homework assignment and, if needed, extra consults for stress reduction are planned before the intervention starts. The OP is further responsible to inform the supervisor about the workplace intervention and to ask for his or her participation. To prevent conflicting advise about RTW the OP sends a letter about the workplace intervention and a communication form to the employee's general practitioner. Like in usual care, the OP provides advice about the date of work resumption.

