### Sample size

Time to lasting RTW is the primary outcome measure for the power calculation. In order to calculate the sample size we assumed that a Hazard Ratio (HR) of 2.0 is the smallest clinical and societal relevant ratio. A HR of 2.0 indicates that employees in the intervention group return to work twice as quickly as employees in the control group. This HR is based on recent studies in occupational health care on RTW of short-term sick-listed employees with low back pain and adjustment disorders[11,25,27,28]. Assuming that a minimum of 2/3 of the participants achieve a full RTW during the follow-up, the calculation showed that a sample size of 98 employees is needed (a power of (1-β =) 0.80 and a two-sided significance level of 0.05 (α)). Since the OPs, because of their role and function in the RTW process, may influence the RTW date, a multilevel analysis on the level of the OP is taken into account. For 13 OPs and an intraclass correlation coefficient (ICC) of 0.05 (clustering in our groups is not presumed to be large) a total of 130 employees are needed. When taking into account a loss to follow-up of 10%, 144 employees have to be enrolled in the study. Although loss to follow-up is taken into account, we do not expect a high loss to follow-up in this study because data about the primary outcome (lasting RTW) will be acquired from the continuous company registration systems after the one-year follow-up.

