### Outcomes

This study has a one-year follow-up with measurements scheduled at 3, 6, 9, and 12 months after baseline. After the baseline measurement, all questionnaires are sent to the employees by mail. Data on absenteeism are registered continuously by the companies and will be acquired from the registration systems after the one-year follow-up. These data will be checked with information in the medical file of each employee in the occupational health services. If the data are not consistent, the OP will be asked for clarification. Data about the diagnoses will be obtained from the medical file of each employee. OPs in the Netherlands classify diagnoses according to the Classification of diseases (CAS)[29] which is based on the ICD-10.

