### Methodological considerations

A limitation of this study is that it is not possible to blind the employees and health care providers for the intervention allocation, because of the nature of the workplace intervention. The data of the primary outcome will be extracted from databases, therefore no bias will be introduced due to non-blinded employees or OPs for this outcome. A strength of this study is that owing to the screening procedure selection bias is restricted, because the OP has no role in the inclusion of participants. However, selection bias may occur due to self-selection of employees.

There is increasing interest in RTW as an outcome in research. However, little agreement exists about the source of the RTW data. A workers compensation database might underestimate sick-listed days compared with self report by the employee [48,49]. Also, several definitions of RTW are available in the occupational health field [50]. The definition of lasting RTW that we use is the most strictest known and could result in the lowest percentage RTW. For a successful RTW it takes into account not only speed but also durability of RTW. However, in a study that compared several RTW definitions, almost the same magnitude of effect of the interventions was found, regardless of the definition used [51].

Furthermore, we are limited to a one-year follow-up of the sick-listed employees with CMDs. From an economic perspective, a longer follow-up is preferable to investigate intervention effects over several years. Also, productivity loss prior and after the episode of sick leave due to CMDs, is not measured in this study. Even if an employee is not absent from work, CMDs can cause a substantial reduction in productivity [52]. For this study, no information can be generated about differences in productivity losses between the workplace intervention group and the usual care group. Brouwer et al. estimated that productivity loss both prior and after the episode of sick leave can lead to an increase in estimated production losses of about 14% [53].

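### Extraction from a database does not prevent all bias from lack of blinding in lasting return-to-work, and a research code does not make the analysis blind

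*Protocol article*

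**What the plan says.** Two sections of the protocol article state that the primary outcome is free of bias from lack of blinding. Blinding: "Since these measurements are extracted from computerized databases, bias caused by a lack of blinding is prevented for this outcome". Methodological considerations, in the Discussion: "therefore no bias will be introduced due to non-blinded employees or OPs for this outcome".

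Other statements bear on that claim:

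- Blinding: "The participants, the occupational health professionals and the researcher are not blinded for the group assignment", and "OPs will be visited by both employees in the workplace intervention group and employees in the usual care group". The same section says that companies register the absence and that the occupational health services manage the register.
- Consult OP: "Like in usual care, the OP provides advice about the date of work resumption".
- Sample size, as the reason for a multilevel allowance: "Since the OPs, because of their role and function in the RTW process, may influence the RTW date".
- Outcomes: register data are checked against the medical file held by the occupational health service, and then "If the data are not consistent, the OP will be asked for clarification".

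On the analysis, the Blinding section describes data entry by a research assistant under a consecutive research code and concludes: "Therefore, the analysis of the data by the researcher will be blind".

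**The concern.** The two no-bias statements are absolute, and the reason given for both is the source of the data. Taking dates from a database stops an outcome assessor from shading them during extraction. It does nothing about how the date came to be what it is, or about what happens when two sources disagree. At both of those points the protocol places an OP who knows the arm.

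At stake is the credibility of the primary outcome in a trial that cannot be blinded. If the statements stand, the report will claim a protection that the design lacks. The one step that could be protected cheaply, the handling of inconsistent dates, may then stay unprotected because the text says no protection is needed. The blind-analysis sentence adds a second assurance that the described procedure does not deliver.

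**Working it through.** **1. The steps that produce the outcome date**

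| Step (section) | Who | Does extraction remove the exposure? |
|---|---|---|
| Advice on resumption date (Consult OP) | OP, unblinded | No. It acts on the real date, in both arms: care delivery |
| Registration of absence (Blinding) | Companies; register managed by the occupational health services | No. The register stores what was decided |
| Extraction of dates (Blinding, Outcomes) | Not stated | Yes. This is all the argument covers |
| Clarification of inconsistent records (Outcomes) | OP, unblinded | No. It follows a disagreement between register and file: ascertainment |

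One row of four is covered. The first and last rows contradict a claim of no bias, by different mechanisms.

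**2. What the plan's allowance for OPs does**

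Inputs, all from Sample size: HR 2.0, two-sided alpha 0.05, power 0.80, event proportion 2/3, 13 OPs, ICC 0.05, 10% loss. Equal allocation follows from Randomisation procedure.

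- Events (Schoenfeld): (1.960 + 0.842)² / (0.25 × (ln 2)²) = 7.849 / 0.1201 = 65.35
- Employees: 65.35 / (2/3) = 98.0
- Design effect: 1 + (98/13 − 1) × 0.05 = 1.327; 98 × 1.327 = 130.04
- Loss: 130 / 0.90 = 144.4

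The stated 98, 130 and 144 reproduce. The step from 98 to 130 is the plan's response to OP influence. It protects against understated variance when employees share an OP. It does nothing about an influence that differs by arm within an OP.

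**3. How much the clarification step could matter**

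The documents give neither the share of inconsistent records nor the size of any change, so both are assumptions. The simulation used 130 employees, 65 per arm, a true HR of 1, exponential times with 2/3 returning within 365 days (rate ln 3 / 365 = 0.0030 per day), no OP clustering, and a Cox model, with 4,000 runs per row. Dates were moved earlier in the intervention arm only.

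| Share of intervention-arm dates moved | Days early | Median HR | Two-sided rejection at 5% |
|---|---|---|---|
| None | 0 | 1.00 | 5.2% |
| 10% | 14 to 28 | 1.00 to 1.01 | 5.0 to 5.4% |
| 25% | 14 to 28 | 1.02 to 1.03 | 5.4 to 5.8% |
| 50% | 28 | 1.06 | 5.4% |
| 100% | 7 / 14 / 28 | 1.03 / 1.07 / 1.13 | 5.1 / 6.1 / 7.8% |

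Simulation error on a 5% rejection rate is √(0.05 × 0.95 / 4000) = 0.35 percentage points, so only the rows with every date moved by 14 or 28 days stand clearly above 5%.

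**4. What one recurrence decision can move**

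Under Effect evaluation, a recurrence within 4 weeks of full RTW belongs to the preceding episode. Counting it moves the event from the first full RTW to the later one:

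shift = (days from first RTW to recurrence, at most 28) + (length of recurrence)

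For example, a 2-day absence starting on day 10 gives 10 + 2 = 12 days. A long recurrence gives more than 28. The 4 weeks cap the gap; they set no minimum on the shift.

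**5. The blind analysis**

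Blinding calls the researcher unblinded and, as its basis for a blind analysis, offers only that data are entered under a research code. A code replaces the name. Whether the arm is masked depends on how the group variable is labelled and who holds the key, and the text says neither. Under Randomisation procedure, the envelopes are offered to each employee by the researcher.

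**The case against.** The strongest reply has four parts.

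*Advice on resumption is care, not measurement.* This stands. It is given in both arms and acts on the real date, and the Discussion openly lists the lack of blinding as a limitation. The Sample size wording is also only that OPs may have influence. But the Discussion sentence excludes any bias arising from unblinded employees or OPs, without limiting itself to measurement, so the contradiction remains.

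*The clarification step is narrow.* This stands too. It applies only to inconsistent records, the text says the OP is asked and not that the OP decides, and detailed handling may sit in a fuller document. What does not belong elsewhere is the assertion, made here, that bias is prevented.

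*The effect is likely small.* For clarification alone the simulation agrees.

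*Unblinded conduct and blind analysis can coexist.* They can, if the arm is masked in the analysis file. The code cited as the reason does not do that.

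Three stronger readings are tempting and are not supported. A reader might infer that differential ascertainment is inherent in the design; nothing in the protocol shows that clarification works differently by arm. A reader might take the 4-week rule to mean that each disputed recurrence moves the event by at least 28 days; the definition does not say so. A reader might suppose that the researchers issue the codes; the protocol does not say who does.

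**Conclusion.** The point holds as a correction to two statements and one procedure. The no-bias sentences in Blinding and in Methodological considerations are wrong as written, because the protocol's own account gives unblinded OPs a part in the real RTW date and in clarifying inconsistent records. What is established is an unprotected route to bias between arms, not bias itself.

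Its size cannot be derived from the documents. Under the assumed shifts of 7 to 28 days, all in one direction and one arm, a null HR moves to about 1.00 to 1.03 when 10% to 25% of dates are affected, and to 1.13 in the extreme case where every date is 28 days early. Both are small beside 2.0. These runs do not cover longer shifts from a long disputed recurrence, nor OP influence on the real date. The sample-size figures are not in dispute.

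The blind-analysis sentence is unsupported by the reason given for it. The correction should be made before the register data are extracted, which the plan places after the one-year follow-up.

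**What to change.** 1. In Blinding and Methodological considerations, limit the claim to bias at extraction, and state that RTW decisions were made by people who knew the allocation. No data rule can remove that part; it can only be declared.
2. Before extraction, write a rule for inconsistent records: which source prevails for the date of full RTW, for partial against full absence, and for whether a recurrence counts. Apply it to extracts with allocation removed. Limit the extracts to dates and absence entries, since the RTW coordinator's reports go to the OP and could reveal the arm if filed (an inference).
3. Run a sensitivity analysis comparing unaltered register dates with clarified dates, and report by arm how many dates changed and in which direction.
4. Either run the primary analysis on a file with masked group labels, with the key held by someone else, or delete the blind-analysis sentence.

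The cost is a short data-handling rule, one extra run of the primary model, and a less favourable statement about blinding. No new data are needed; the research assistant who already enters the data could remove the allocation. Unaltered register dates are not proposed as a cure, because the register also stores unblinded decisions.

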### Co-interventions and compliance

Co-interventions can not be avoided, because less employees will participate when asking to stop with or stay away from other treatments. In both the intervention and control groups co-interventions are assessed in each follow-up measurement. The data about co-interventions on baseline can be used to adjust for co-interventions in the final multivariate analyses if necessary. In the intervention group the compliance to the workplace intervention will be measured by asking employees, supervisors, OPs and RTW coordinators independently about the intervention applied.

### Contamination

As randomisation is performed at the level of the employee, OPs who are trained in the workplace intervention guide participants in both the workplace intervention group and the usual care group. However, the actual intervention will be applied by RTW coordinators. They are asked to avoid application of components of the workplace intervention in case of guidance of employees who are in the usual care group. To prevent contamination and role confusion, RTW coordinators will not apply the workplace intervention for employees from departments they work for regularly.

### Outcomes

This study has a one-year follow-up with measurements scheduled at 3, 6, 9, and 12 months after baseline. After the baseline measurement, all questionnaires are sent to the employees by mail. Data on absenteeism are registered continuously by the companies and will be acquired from the registration systems after the one-year follow-up. These data will be checked with information in the medical file of each employee in the occupational health services. If the data are not consistent, the OP will be asked for clarification. Data about the diagnoses will be obtained from the medical file of each employee. OPs in the Netherlands classify diagnoses according to the Classification of diseases (CAS)[29] which is based on the ICD-10.

#### Effect evaluation

The primary outcome measure in this study is lasting RTW, defined as: duration of sick leave with CMDs in calendar days from the day of randomization until full RTW in own or other work with equal earnings, for at least 4 weeks without (partial or full) recurrence. This means that recurrences of sick leave within 4 weeks of full RTW are considered as belonging to the preceding period of sick leave.

Secondary outcome measures are:

- Total number of days of sick leave. These will be calculated for the entire follow-up period.

- Severity of CMD symptoms. Changes in symptoms of distress, depression, anxiety, and somatization are measured by the Four-Dimensional Symptom Questionnaire (4DSQ). The 4DSQ is a valid self-report questionnaire to measure distress, depression, anxiety and somatization in a working population [17,23].

- Coping style. This outcome is measured with the Ways of Coping Questionnaire (WCQ) [30], which is based on Lazarus' Theory of Stress and Coping[31]. Only two dimensions of the WCQ are included. These dimensions are avoidance and planful problem-solving, to evaluate whether the workplace intervention influences these ways of coping.

- Job content. The Job Content Questionnaire (JCQ)[32] is used to measure job content at baseline and 3 months. Job content data can either be prognostic or provide insight in working mechanism of the workplace intervention.

- Attitude, Social influence and self-Efficacy (ASE) determinants. The ASE-model could provide insight into the working mechanism of the workplace intervention [9]. Questions about attitude, social influence, self-efficacy, and barriers and facilitators were formulated, based on a validated structure of the questions often used in health promotion research[33,34] and are incorporated in the questionnaire at baseline and after 3 months. The questions are measured on bipolar five-point Likert scales.

#### Prognostic measures

Sick leave in the past year, burnout and expectations of the employee about the duration of absence[35] are considered to be potentially prognostic for RTW. Burnout is measured by the Utrecht Burnout Scale-General Survey UBOS[36], the Dutch version of the Maslach Burnout Inventory [37]. In addition, the amount of psychosocial problems may be a prognostic factor for CMDs and sick leave. Psychosocial problems over the last 6 months are measured by the BIOPRO questionnaire [38].

#### Cost-effectiveness evaluation

Cost-effectiveness will be evaluated from the societal perspective. Direct costs of health care usage are measured by the Tic-P questionnaire [39]. The Tic-P is developed for medical costs relevant to the treatment of mental health disorders, such as visits to general practitioner, occupational physician, psychologist, psychiatrist, social worker, admission into a hospital, use of medication etc. Health care costs will be valued according to the prices suggested in the guidelines for economic evaluation in The Netherlands[40]. If cost-guidelines are not available, costs will be estimated using real prices or population-based estimates if available in the literature. Costs of lost productivity caused by (partial) sick leave due to CMDs are calculated from the number of days of sick leave and lost earnings, as provided by the occupational health services. Indirect costs can be calculated using the friction cost approach and the human capital approach, based on income as provided by the employee or as derived from function, age and gender. To compare the results of the cost effectiveness analysis with other conditions, general health status is measured according to the standard Dutch version of the EuroQol EQ-5D[41].

#### Process evaluation

A process evaluation is conducted for the first 35 employees who actually received the workplace intervention. A questionnaire is sent to their supervisor, the OP and the RTW coordinator as well. For employees, the questionnaire is included in the postal questionnaire after 3 months and contains questions about employee satisfaction, the work adaptations chosen, the expected effect of work adaptations, and the compliance with workplace intervention process. Employee satisfaction is measured with the short version of the Patient Satisfaction with Occupational Health Services Questionnaire (PSOHQ)[42]. In addition, the barriers for RTW, the solutions and the RTW plan discussed in the meetings are collected within standardized schemes. All identified barriers for RTW and solutions will be analyzed qualitatively and classified by two researchers independently. The classification will be based on a simplified version of the 'Ergonomic Abstracts' classification scheme [43,44].

### Statistical analyses

All statistical analyses will be performed at employee level, according to the intention-to-treat principle. In order to assess whether protocol deviations have caused bias, the results of the intention-to-treat analyses will be compared to per protocol analyses, excluding those employees who were not treated according to the intervention protocol. Baseline characteristics of employees in the two groups will be compared using descriptive statistics. If necessary, analyses will be adjusted for prognostic dissimilarities.

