### Participants

The source population (n ≈ 20.000) consists of blue and white collar employees working in the University, the University Medical Center and the steel factory. The source population is diverse: the healthcare sector, the industrial sector and administrative sector are all involved in this study. The workplace intervention is assumed to be appropriate for all these sectors.

The employees eligible for this study are on sick leave from regular work for 2 to 8 weeks with CMDs. CMDs encompass both criteria-based psychiatric disorders (mostly depressive and anxiety disorders) and 'subthreshold' disorders (including adjustment disorders)[16]. Employees with CMDs are selected on the basis of elevated distress levels and sick leave. Distress reflects the effort people have to put into coping with stressors in order to maintain their habitual level of psychosocial functioning[17]. Severe distress, however, may lead to a breakdown in coping, resulting in psychosocial disfunctioning (e.g. sick leave). It is generally known that distress and depression coexist with chronic diseases and/or physical symptoms [18-21], therefore a heterogeneous group of participants will be selected.

Employees are in the working age range, 18 to 65 years old. Exclusion of employees occurs in case of 1) a conflict between the employee and the employer with legal involvement; 2) working less than 12 hours a week; 3) pregnancy; 4) sick-listed for more than 8 weeks; 5) another episode of sick leave within one month before the current episode; 6) inability to complete questionnaires written in the Dutch language. After randomisation the occupational physician (OP) is responsible to prevent employees with severe psychiatric disorders (mania, psychosis or suicidal) and employees with a terminal illness from starting the workplace intervention.

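### The per-protocol comparison cannot show whether protocol deviations caused bias, because its exclusion rule in practice acts on the intervention arm only

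*Protocol article*

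**What the plan says.** All analyses follow ITT (Statistical analyses). The same section adds a PP analysis and gives it one purpose: "In order to assess whether protocol deviations have caused bias, the results of the intention-to-treat analyses will be compared to per protocol analyses". It gives one rule for membership: the ITT results "will be compared to per protocol analyses, excluding those employees who were not treated according to the intervention protocol". It states no corresponding rule for usual care.

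Four other places bear on who is removed:

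- **Co-interventions and compliance:** "In the intervention group the compliance to the workplace intervention will be measured by asking employees, supervisors, OPs and RTW coordinators independently". Compliance is not measured in the usual-care group.
- **Participants:** "After randomisation the occupational physician (OP) is responsible to prevent employees with severe psychiatric disorders (mania, psychosis or suicidal" and, in the same sentence, "employees with a terminal illness from starting the workplace intervention". These conditions are not among the six numbered exclusion criteria that the researcher checks by telephone before randomisation. The OP's action keeps the employee out of the intervention, not out of the trial.
- **Consult OP and Organizational preparation:** the meetings follow an OP consult, the supervisor's agreement and the planning of three meetings. If needed, "extra consults for stress reduction are planned before the intervention starts".
- **Effect evaluation (under Outcomes):** the primary outcome is counted from the day of randomisation, so the interval before the first meeting is already follow-up time.

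**The concern.** Comparing PP with ITT can inform on bias only if the PP contrast is itself free of selection. Here it is not, for two reasons.

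First, the exclusions are one-sided. Only someone allocated to the intervention can fail to be treated according to its protocol.

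Second, they are tied to prognosis, in two opposing ways. Employees held back for severe psychiatric disorder or terminal illness are likely to return late. Removing them from one arm favours the intervention. Employees who return before the meetings are by definition fast returners, and removing them from one arm works against it.

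A gap between PP and ITT can therefore be produced by the exclusion rule alone, and two opposite selections can leave no gap. In neither case does the comparison answer the question set for it. At stake is a published check on the primary result that could cast doubt on a sound ITT estimate or give unearned reassurance.

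**Working it through.** **The plan's own figures.** The sample-size chain is not in dispute and only sets the scale.

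- Events: (1.960 + 0.842)² / (0.25 × (ln 2)²) = 65.3. Divided by 2/3, this gives 98.0 employees (stated: 98).
- Clustering: 1 + (98/13 − 1) × 0.05 = 1.327, and 98 × 1.327 = 130.0 (stated: 130).
- Loss: 130 / 0.9 = 144.4 (stated: 144), or about 72 per arm.

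**Inputs for the check**

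- *From the plan:* 2/3 return to work (RTW) overall and HR 2.0. With q the control proportion not returned at one year, (1 − q) + (1 − q²) = 4/3, so q² + q − 2/3 = 0 and q = 0.457. Control RTW is 54.3%. The exponential rate is −ln 0.457 = 0.782 per year, or 0.00214 per day.
- *Assumed, because the documents do not give them:* share held back f = 5%, 10% or 20%; their RTW hazard r = 0.3 to 0.5 of the others'; intervention start spread evenly over 2 to 6 weeks after randomisation.
- *True HR:* 1.0, with the same mix of employees in both arms.

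**Mechanism 1: employees held back leave the intervention arm only.** At time zero the usual-care hazard is the others' hazard times 1 − f(1 − r), so the PP HR starts at 1 / (1 − f(1 − r)). For f = 10% this is 1/0.95 = 1.05 at r = 0.5 and 1/0.93 = 1.08 at r = 0.3. It then grows, because slow returners accumulate among usual-care employees still off work. A Cox model fitted to large simulated samples over the full year gives:

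| Held back (f) | PP HR, r = 0.5 | PP HR, r = 0.3 | ITT HR |
|---|---|---|---|
| 5% | 1.03 | 1.05 | 1.00 |
| 10% | 1.06 | 1.10 | 1.00 |
| 20% | 1.13 | 1.21 | 1.00 |

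**Mechanism 2: early returners leave the intervention arm only.** With a mean start at 28 days, 1 − exp(−0.00214 × 28) = 5.8% of the arm has already returned. That is 5.8 / 54.3 = 10.7% of its events. The arm's HR is near 0 in that window and 1 afterwards, so the average is about 1 − 0.107 = 0.89. The simulation agrees (0.89 to 0.90).

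**Both together.** The PP HR runs from about 0.92 (f = 5%, r = 0.5) to about 1.08 (f = 20%, r = 0.3). At f = 10% it is 0.95 to 0.98, where the two selections nearly cancel.

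**Control check.** A second simulation set RTW at 2/3 in both arms. When the same type of employee was removed from both arms, the HR stayed at 1.00 within 0.01. The shift comes from one-sided removal, not from removal as such.

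**The case against.** The strongest reply has four parts.

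**Membership of the PP set is inferred.** The article does not say that exclusions fall on one arm. An employee held back by the OP is being handled as the protocol directs, and might not be counted as a deviation. Nor does the article say that early returners are excluded. A full analysis plan could settle this. That stands as a limit on certainty. But the printed rule turns on not having been treated according to the intervention protocol, compliance is measured in one arm, and no usual-care rule appears. One-sided removal is the natural reading.

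**The effect is small against the trial's precision.** With 2/3 × 144 = 96 events, the standard error of the log HR is about 2/√96 = 0.20, so a 95% interval spans a factor of about exp(1.96 × 0.204) = 1.5 each way. In the simulation with 2/3 RTW in both arms and 72 per arm, the PP test at r = 0.5 rejected a true null in 4.7% of trials with 5% held back and 6.0% with 10%. This stands, and it limits the seriousness. It does not rescue the stated purpose, since the comparison still cannot tell bias from selection.

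**A reader might infer that PP status will be known only for some employees**, because "A process evaluation is conducted for the first 35 employees who actually received the workplace intervention". The documents do not support that. This limit belongs to the process evaluation. The Co-interventions and compliance section has compliance measured in the intervention group from four sources, with no such limit.

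**A reader might also conclude that the OP's check should move ahead of randomisation.** That conflicts with the Methodological considerations section, which counts it a strength that the OP plays no part in inclusion.

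**Conclusion.** The concern holds for the supporting comparison and its stated purpose. As written, a PP-ITT difference does not show that deviations caused bias, and agreement does not show that they did not.

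The size depends on assumptions. With a true HR of 1.0, employees held back move the PP HR to about 1.03-1.05 (5%), 1.06-1.10 (10%) or 1.13-1.21 (20%). Early returners move it to about 0.89, and both together give about 0.92-1.08. The documents supply neither the share held back, nor its prognosis, nor the time to the first meeting. If few are held back, the first mechanism is minor. The net direction cannot be predicted.

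Two stronger readings are tempting. One is that the primary result is biased. It is not affected, because ITT keeps everyone as randomised and no decision rests on the PP set. The other is that the PP analysis will be grossly misleading. HRs of 1.52 or 2.12 do arise in the simulation with 2/3 RTW, but only if 20% or 30% of the arm is held back and none of them returns. Nothing in the documents points to such shares.

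This should be fixed, but the trial's main conclusion does not depend on it.

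**What to change.** 1. Keep ITT as the sole basis for the effect. Delete the statement that the PP comparison assesses whether deviations caused bias, and label any PP table descriptive.
2. In that table, remove the severe-disorder and terminal-illness group from both arms, identified from the medical-file diagnoses that the Outcomes section already has collected for every employee. This does not cure the early-returner selection, so the descriptive label is still needed.
3. Add, as a sensitivity analysis, a complier-average estimate with allocation as the instrument, using the compliance data planned for the intervention group. It is simplest on a difference scale: for example, the ITT difference in total days of sick leave divided by the proportion of the intervention group that started the intervention, taking usual care as having no access to it.
4. State the exclusion restriction behind item 3 as an assumption. It is open to doubt, because the pre-intervention OP consult adds a stressor inventory and contact with the supervisor and general practitioner, which may affect employees who never start.

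The cost is a few sentences of plan wording and a little more analysis. No new data collection is needed, and recruitment, randomisation and clinical criteria stay as they are.
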